**Type of study:**

Pilot RCT, Investigator-led

**Introduction:**

**The Problem:** As of 23^rd^ April 2020, there have been over 3 million confirmed cases of SARS-CoV-2 infections resulting in more than 200,000 deaths worldwide (1), most commonly due to severe pneumonia causing multi-organ failure (2). Whilst, to date, there have been 81 deaths in Australia amongst around 6,000 COVID-19 diagnosed positive patients, this number is anticipated to continue to increase in the next few weeks (1). Patients infected with SARS-CoV-2 virus present with varying degrees of symptoms, including mild to moderate symptoms (81%), the disease state called COVID-19 (14%) similar to a cold or flu and, in severe cases, 5-6% of confirmed patients progress to lower respiratory tract infection, severe pneumonia, respiratory failure, shock and multi organ dysfunction, including ARDS (2). A recent WHO analysis has confirmed that many patients have become critically ill with severe pneumonia and that this is the primary cause of death for these patients (3). Currently, approximately 1% of confirmed cases in Australia will die. Although the spread of the virus is being mitigated to some extent in Australia, infectious disease clinicians advise that the pandemic will remain active for several months to come, while a “second wave” of infections is anticipated once restrictions on movement are relaxed.

**Background:** Almost all serious consequences of COVID-19 feature pneumonia. When SARS-CoV-2 enters the lungs, it triggers the body’s immune response to attack the virus, resulting in localised inflammation. Increasing evidence suggests that a subgroup of these patients, with severe COVID-19, may develop ‘**cytokine storm syndrome’**, an overreaction of the body’s immune system to the virus caused by localised production of inflammatory factors (cytokines) by infiltration of inflammatory cells. The localised inflammatory response can result in hyper-inflammation causing serious harm to affected organs resulting in multi-organ failure and, if untreated, the cytokine storm syndrome, which is usually fatal (4).

**The Need:** There is a major unmet need for a safe and effective treatment for COVID-19 infected patients, especially in moderate to severe cases of pneumonia. Avoiding the “cytokine storm” may be a key factor for the treatment of severe COVID-19 infected patients. A range of techniques are being investigated to mitigate the damage caused by moderate to severe pneumonia due to SARS-CoV-2 (4), before it becomes life threatening. Many are still in the early stages of development and there are, thus, currently no proven therapies for COVID-19 related severe pneumonia; meaning the management of the condition has been primarily related to organ failure support, including mechanical ventilation for worsening respiratory failure (4). A more general approach, targeting the hyper-inflammatory reaction, along with immunomodulation of an over reactive immune system, rather than use of either anti-virals or specific cytokine inhibitors or anti-inflammatory medications alone may provide greater benefit to these patients. **Umbilical Cord Blood (UCB) derived cell therapy with proven anti-inflammatory and immunoregulatory properties may provide such a therapeutic option.**

**Rationale:**

**Umbilical Cord Blood derived cells:** UCB is a rich source of Haematopoietic Stem Cells (HSCs) that have been used in clinical therapy (transplantation) to treat haematological disorders for over 30 years (5) and, in Australia, over 500 UCB units have been released to treat a variety of approved conditions (6). Although UCB has been used primarily, as a source of haemopoietic stem cells, more recent evidence suggests that it is a therapeutically important source of other cell populations with **anti-inflammatory, immune-regulatory and vasculogenic properties**. These include not only mesenchymal stromal cells (MSCs) but also endothelial progenitor cells and immature immune cells, including potent Myeloid-Derived Suppressor Cells (MDSCs) and T-Regulatory cells (Tregs) both of which can be readily expanded from UCB (7, 8). There are currently over 60 registered clinical trials underway worldwide investigating the potential of UCB cells to act as a regenerative treatment for an expanding and diverse list of medical conditions (9), with multiple units already being released from private cord blood banks for regenerative medicine applications (10). This includes releases from Cell Care (a private cord blood bank) for use in Australia’s first clinical trial of cord blood infusion as a possible treatment for cerebral palsy and of Type 1 Diabetes (9).

Several very recent studies have reported the use of MSCs, derived from multiple sources, in COVID-19 applications (11, 12) and clinical trials of Umbilical Cord derived MSCs are planned (clinicaltrials.gov, “COVID-19” & “MSC” & “lung”). We believe that **UCB derived cell administration will value add to the potential efficacy observed with MSCs alone**, particularly during the moderate to severe phase of the disease. Unlike adult tissue sources of MSCs like adipose tissue and bone marrow, in which MDSCs and Tregs are barely detectable, significant proportion of these immunomodulatory cells are found in umbilical cord blood where they balance fetal immune responses and prevent aggressive inflammatory responses (13). The MDSC population represents an innate immune cell subset, composed of a heterogeneous mix of early myeloid progenitors, immature granulocytes, type-2 macrophages, pre-mast cells and immature dendritic cells at different stages of differentiation and characterised by its capacity to suppress T cell immunity. Besides being an excellent source of immune cells for controlling immune-regulated destruction of endogenous cells, such as that observed in prevention of destruction of beta cells in type 1 diabetes (9), UCB cells provide a treatment modality to address inflammatory reactions in the brain as observed in cerebral palsy, autism and following acute brain injury (5). Preclinical studies are now emerging on the use of UCB in the treatment of respiratory conditions (see below) and there are currently 22 trials listed in “ClinicalTrials.gov” for use of umbilical cord blood in respiratory conditions in neonates and adults (“Respiratory” & “Umbilical Cord Blood”).

**Pre-clinical and clinical studies:** We have used animal models of preterm and perinatal conditions to show that UCB derived cell administration is protective, as well as facilitating tissue repair and regeneration following injury. We have demonstrated, in multiple studies, that these effects are mediated via their **anti-inflammatory, immuno-modulatory, anti-apoptotic, and growth factor support**, rather than by direct cell replacement. We have also shown that these cells protect vasculature and stimulate vasculogenesis by release of vasogenic factors (14). Specifically, with respect to the lung, we have shown that UCB treatment in ventilated lambs increased angiogenesis, as evidenced by increased Vascular Endothelial Growth Factor expression and vessel density, attenuated immune cell infiltration into lungs and modulated the injurious effect of Ventilation Induced Lung Injury (15). In addition, we have demonstrated that administration of UCB derived cells could have beneficial effects by **preventing or attenuating the cytokine storm** since we have shown that these cells down-regulate TNF-alpha, a key inflammatory cytokine, release following a lipopolysaccharide (LPS) induced inflammatory challenge (16). Further studies in murine neonatal and adult models of have reported on the effects of human UCB derived cells on respiratory physiology i.e. reduction of central airway resistance to normoxic levels and improvement of alveolarisation, lung compliance and elastance (17, 18). Treatment also inhibited lung vascular injury, evident by decreased lung vascular permeability, attenuation of expression of pro-inflammatory mediators and, importantly with respect to this proposal, lung inflammation was returned to normal levels after an inflammatory LPS challenge, causing a marked increase of survival rate (18). **Taken together, these preclinical data clearly demonstrate the protective effects of UCB derived cells on acute lung injury.**

UCB cells have been widely used in multiple non-haematopoietic cell-based therapies. Our group has been directly involved in the first Phase 1 Trial of the use of UCB in treatment of confirmed cerebral palsy in children in Australia (SCUBI Trial (19) and, recently, we obtained ethics approval to administer autologous UCB cells to extremely preterm neonates in a Phase 1 Safety and Feasibility Trial (CORD SaFe Trial, ACTRN12619001637134) using our Cell Therapy Platform, at the Monash Health Translation Precinct, MHTP, to prepare UCB cells released from Cell Care for clinical use. It has been demonstrated that, after intravenous infusion, the majority of UCB derived cells accumulate in the lung, the “pulmonary first passage effect”, which is also the major site of SARS-CoV-2 virus entry and consequent lung inflammation (20, 21). In addition, exciting new evidence, in several recent reports, demonstrate that the first step of COVID-19 pathogenesis is that the virus specifically recognises the angiotensin I converting enzyme 2 receptor (ACE2) by its spike protein. Spike protein priming is also essential for the host cell entry and spread. ACE2 is a co-receptor for viral entry for SARS-CoV-2; and ACE2 has a broad expression pattern in the human body, with strong expression in type II alveolar cells in the lungs (22). The lung is, thus, an obvious choice for therapeutic intervention in COVID-19. **Since UCB derived cells have immunomodulatory, in addition to anti-inflammatory, effects, localisation of reparative UCB cells to the lung should improve the pulmonary microenvironment, protect alveolar epithelial cells, prevent pulmonary fibrosis and improve lung function**.

**Expansion of UCB cells:** While we are confident that UCB cells will result in improvement of pulmonary function in COVID-19 infections, we are concerned that we will be able to source sufficient unexpanded UCB units to treat severe cases of COVID-19 infections in the immediate short term. Consequently, cord blood science in general, and our lab in particular, has focused on the ability to expand the number of cells in cord blood to boost utility in both current and future medical uses, i.e. in transplantation, in immune therapy and in regenerative medicine. In collaboration with Cell Care Australia, we have developed (23), modified and undertaken in vitro and in vivo preclinical studies of expanded UCB derived cells that reliably and reproducibly results of not only a higher number of haematopoietic stem cells but also progenitor cells, T-cell precursors and MDSCs (including pre-dendritic and pre-mast cells) that display highly potent immune-regulatory capacities. These observations are in line with the observations made during clinical trials of expanded cord blood transplantation for haematological malignancies (24, 25).

Expanded UCB derived cells have already been shown to attenuate inflammatory lung injury (18) and the expansion technology has received Orphan Drug Designation (FDA, Dec 2018) in the US. Using commercially available systems, it permits expansion of cord blood units 100-fold within 7 days and over 1,000-fold following a further 7-day incubation. This would provide ample expanded cells for our trial and could permit production of sufficient cells for multiple dosing of patients in the future. Expanded UCB cells are currently undergoing Phase 2 trials in the US and Canada (24) and results of a Phase I/II trial of cord blood transplantation of expanded UCB cells have recently been published (25). These observations underline the potential benefits attributed to the immune-regulatory cells in the expanded cell population, as demonstrated by the reduction of the risk to severe acute and chronic GVHD (25).

**Methods:**

**Aims:** The objective of this proposal is to undertake a pilot, feasibility RCT of a cell-based therapy for treatment of patients infected with SARS-CoV-2 virus related pneumonia to prevent progression to severe ARDS**.** The goal is to roll out an adequately powered, double-blind, randomised controlled trial after this pilot RCT.

**Hypothesis:** Expanded UCB derived cell therapy will be feasible, well tolerated and show potential efficacy in the treatment of acute COVID-19 related moderate to severe pneumonia as a result of their powerful anti-inflammatory and immunomodulatory properties.

**Collection and Expansion of UCB cells:** UCB is already being collected (from healthy pregnant volunteers at term gestation) and processed under strict TGA guidelines. The frozen UCB units will be sourced from Cell Care’s cord blood banks and released to our PC2 and certified grade D, ISO 9001 accredited Cell Therapy Platform Facility at the Monash Health Translation Precinct where they will be thawed, expanded using our expansion system and prepared for IV administration to eligible consented patients.

Once expanded, the cells will be fully tested, for microbes and cell viability, aliquoted and frozen using our GMP compliant, standard operating procedure (SOP) for cell expansion that is being developed. Prior to infusion, the requisite number of cells will be thawed and prepared for infusion. All SOPs for collection, processing, characterisation, storage, release, and preparation for infusion are currently in place for use of UCB cells for another current UCB trial that we are undertaking (CORD SaFe Trial, ACTRN12619001637134).

*Study design*

Pilot, safety and feasibility, randomised controlled trial.

*Blinding and Randomisation*

This will be an unblinded study, given that it is the first of its kind study (using expanded UCB cells) in COVID-19 patients. There will be no placebo infusion. Randomisation will be done by lead PI using computer generated allocation to intervention/ control groups (in blocks of 6 patients) by using sealed opaque envelopes prepared by an independent research nurse.

***P****opulation*

*Inclusion Criteria*:

Hospitalised patients with confirmed SARS-CoV2 infection (based on appropriate nucleic acid or other testing) meeting the following three criteria:

1. Expected to remain an in-patient for at least 48 hours,
2. Features consistent with viral pneumonia on Chest CT or X-Ray (in the opinion of the investigator), and
3. Are unable to maintain a peripheral oxygen saturation of 95% or greater in room air

*Exclusion Criteria:*

1. Patients with known allergies to stem cell preparations.
2. Patients with known significant lung disease before COVID-19 presentation.
3. Patients receiving invasive/ mechanical ventilatory support.
4. Patients with underlying disease, comorbidities or clinical status that, in the opinion of the investigator, suggests death is imminent and/or likely to occur in the next 48 hours.
5. Patients currently on other investigational cell therapies.
6. Patients with known pregnancy.
7. Patient unable to provide consent.
8. The treating team deems that enrolment in the study is not in the best interests of the patient.

***I****ntervention group (n=12)*

Intravenous injection of expanded UCB cells at a dose of 5 million cells/kg. Maximum dose of 500 million expanded UCB cells. Standard supportive care will continue as needed.

The cell number/dosage should be easily achievable with the expansion technology that we have developed and reflects cell numbers currently being used in other COVID-19 MSC trials (12). Cell infusion will occur over 30-60 minutes through a peripheral intravenous cannula.

***C****omparison group (n=12)*

Standard supportive care will continue as needed*.*

***O****utcomes*

*Primary Outcomes:* Safety and tolerability of UCB cell administration (absence of immediate and short-term negative side effects); clinical improvement on a seven-category ordinal scale.

The seven-category ordinal scale consists of: 1, not hospitalised with resumption of normal activities; 2, not hospitalised, but unable to resume normal activities; 3, hospitalised, not requiring supplemental oxygen; 4, hospitalised, requiring supplemental oxygen; 5, hospitalised, requiring humidified nasal high-flow oxygen therapy, non-invasive mechanical ventilation, or both; 6, hospitalised, requiring invasive mechanical ventilation, ECMO or both; and 7, death. This ordinal scale has been used in previous Influenza and some COVID-19 trials (26, 27).

*Secondary Outcomes:* Time to clinical stability (defined as the time from study randomisation until resolution of symptoms leading to discharge from hospital), individual symptom resolution, chest imaging changes (if available), need and duration of mechanical ventilation, incidence of secondary culture positive bacterial infections, and all-cause mortality (30- and 90- day). Immune response will also be studied using assay of inflammatory factors (IL-1b, IL-6, TNF-α and IL-10) from blood samples obtained prior to UCB cell infusion and at 1- and 7-days post infusion.

***T****imeframe*

6-12 months.

*Sample size and statistics*

As this is a pilot, feasibility RCT, a convenience sample size of 12 in each arm has been decided. Further, given the pilot nature of this RCT, significant efficacy is not expected, and hence only descriptive and interpretive statistics will be performed to compare groups as appropriate. This trial will help design an appropriately powered larger trial if treatment is well tolerated.

*Monitoring*

Regular vital monitoring for 24 hours post cell infusion will be conducted as detailed in the case report form.

Daily clinical evaluation of symptoms and classification according to the 7-category ordinal scale until one of the following time points: a) resolution of clinical symptoms b) death. In the hospital, this monitoring will be performed by review of the Electronic Medical Record and discussion with the treating team (unless an investigator is a member of the treating team and has direct contact with the patient). In the community, this will be performed by regular telephone contact. Follow up for other morbidities with 30- and 90-day telephonic contact will also be undertaken.

Routine blood tests, including full blood examination, C-Reactive Protein, liver and renal function, coagulation profile will be done as per treating clinical team directions.

Blood tests for immune response will be done before, and 24 hrs and 7 days after UCB cell infusion.

*Safety Reporting*

*Categorising safety related events:* Events will be categorised as per the National Health and Medical Research Council 2016 recommendation:

**Adverse event (AE)** Any untoward medical occurrence in a patient or clinical trial participant administered a medicinal/ biological product and that does not necessarily have a causal relationship with this treatment.

**Adverse Reaction (AR)** Any untoward and unintended response to an investigational medicinal/ biological product related to any dose administered.

**Serious AE/AR (SAE/SAR)** Any adverse event/adverse reaction that results in death, is life-threatening, requires hospitalisation or prolongation of existing hospitalisation, results in persistent or significant disability or incapacity.

**Suspected Unexpected Serious Adverse Reaction (SUSAR)** An adverse reaction that is both serious and unexpected.

*Data Safety Monitoring Board (DSMB)*

An independent DSMB is being formed comprising of an intensivist, an infectious disease physician, and a scientist familiar with cell-based therapies to review all AE/ AR/ SAE/ SAR/ SUSARs and pre-decided reporting times (interim and final). Adverse incidents will be reported to the DSMB within 1 week of occurrence.

*Reporting to HREC*

The following reports will be submitted to HREC:

1. Any adverse event/ reaction deemed suitable by DSMB to temporarily halt the trial pending review.
2. An interim report after recruitment of 12 patients.
3. Any updates to protocol/ PICF.

*Data management*

Data will be collected prospectively by trial investigators and sourced from bedside clinical charts, monitors, electronic medical records and direct patient feedback. Data will be collected on a paper CRF and recorded in an electronic database. Paper records will be stored in a locked filing cabinet and electronic records will be kept on password protected documents. Data will be stored for 15 years.

*Ethics and oversight*

The clinical trial will be conducted in compliance with the protocol approved by Monash Health HREC and with the NHMRC National Statement on Ethical conduct in Human Research 2007 (updated May 2015). Fully informed, written consent will be obtained as per the participant information and consent form. Participation will be voluntary and option of withdrawal from trial will be possible at any stage. The trial will be overseen by investigator team members drawn from our ICU and infectious diseases teams, while the lead PI will have overall trial oversight and interaction with the DSMB and HREC.

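### Exclusion 6 bars only known pregnancy, and the protocol gives no way of establishing pregnancy status before randomisation or infusion

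*Protocol*

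**What the plan says.** In the protocol's Methods, the sixth exclusion criterion is "Patients with known pregnancy". No other eligibility text concerns pregnancy. The inclusion criteria admit "Hospitalised patients with confirmed SARS-CoV2 infection (based on appropriate nucleic acid or other testing) meeting the following three criteria". Those three criteria concern expected length of stay, imaging and oxygen saturation; none refers to sex, age or childbearing potential.

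Two sets of blood tests are named under Monitoring. The first is clinical: "Routine blood tests, including full blood examination, C-Reactive Protein, liver and renal function, coagulation profile will be done as per treating clinical team directions". The second belongs to the trial: "Blood tests for immune response will be done before, and 24 hrs and 7 days after UCB cell infusion". Neither names a pregnancy test.

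The last exclusion is a general judgement clause: "The treating team deems that enrolment in the study is not in the best interests of the patient".

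Safety and tolerability of the infusion form part of the primary outcome, and 12 patients are to be infused.

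**The concern.** By listing pregnancy as an exclusion, the protocol has decided that pregnant patients should not enter. The word *known* makes that protection depend on what the patient or team already knows. Early pregnancy is a condition that may not yet be known. A site can follow the rule exactly and still admit a patient whom it is meant to keep out.

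At stake is an avoidable exposure to an immunomodulatory cell product in a small trial with a safety objective. The protocol's later steps are poorly placed to pick it up. The serious-event definition under Safety Reporting does not name pregnancy or a fetal outcome. The last planned contact is a telephone call at 90 days, which would come before the end of a pregnancy that was early at infusion. Screening is the point at which the protocol can act.

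**Working it through.** The protocol states no figure to reproduce; the sample size is a convenience sample. The check is a reading of the text, followed by an illustration of size.

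**Step 1: take a patient with an unrecognised early pregnancy through the criteria.**

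- Inclusions 1 to 3 (expected stay, imaging, oxygen saturation): pregnancy status has no bearing on any of them.
- Exclusions 1 to 5 (allergy to stem cell preparations, prior lung disease, invasive ventilation, imminent death, other investigational cell therapy): none depends on pregnancy.
- Exclusion 6: not met, because the pregnancy is not known.
- Exclusion 7 (unable to consent): unrelated.
- Exclusion 8 (treating team's judgement): it could be used, but only on facts the team has, and nothing asks the team to establish this one.

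The patient is eligible, can be randomised and, if allocated to the intervention, can be infused.

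**Step 2: look for a test that would make the pregnancy known.** The named clinical tests are full blood examination, C-reactive protein, liver and renal function, and coagulation, all at the treating team's discretion. The trial's own samples are for inflammatory factors. The eligibility, intervention, monitoring and safety sections contain no pregnancy test and do not mention childbearing potential or contraception.

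**Step 3: check whether an existing sample could be used.** The first immune-response sample is timed before infusion, not before randomisation. Routine bloods are at the treating team's direction. The protocol therefore guarantees no trial sample before randomisation.

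**Step 4: illustrate the size.** The documents give no sex or age mix, so both inputs are assumptions.

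- Assume *W* = 2 to 5 of the 24 patients are women who could be pregnant.
- Allocation is 12:12, so the expected number infused is *W*/2 = 1 to 2.5.
- Assume a proportion *p* = 0.5% to 2% of them have an unrecognised pregnancy.
- Expected exposures = (*W*/2) × *p*: from 1 × 0.005 = 0.005 to 2.5 × 0.02 = 0.05.

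For values this small, the chance of at least one exposure is nearly the same as the expected number: about 0.5% to 5%. If one did occur, it would be 1 of 12 infused patients (8.3%).

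**The case against.** The strongest reply is that the text shows less than a reader might infer from it.

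- *No test is planned.* The document does not show this. The case report form and the consent form are not in the text reviewed, the list of routine bloods is not exhaustive, and it sits under Monitoring, not screening. A hospital may also test as routine care. What can be said is that the protocol specifies no test. That is enough, because eligibility is a protocol matter and routine care is not a trial requirement.
- *The product is new to humans.* The protocol's phrase is "first of its kind study (using expanded UCB cells) in COVID-19 patients". It describes the study in this disease and is given as a reason for not blinding. The Rationale reports expanded cord blood cells already in trials elsewhere. That the cells are allogeneic is a fair inference from their donor source, but the protocol does not use the word for this product.
- *One exposure would halt the trial.* This is speculation. Under Reporting to HREC, a halt follows an adverse event or reaction that the DSMB considers to warrant one, and exposure in pregnancy is not itself in the serious-event definition. Nor does the document describe any fetal or maternal risk from these cells.
- *Known is simply the house style.* Exclusions 1 and 2 use the same word for allergy and lung disease, and nothing in the text is contradicted. This is fair as a reading of the drafting. But those two are ordinarily matters of history, whereas an early pregnancy may be absent from the history and a simple test can detect it.

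These limits narrow the wording. They do not close the gap.

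**Conclusion.** The point holds in this form: exclusion 6 covers only known pregnancy, the protocol specifies no means of establishing pregnancy status before randomisation or infusion, and an unrecognised pregnancy therefore passes every criterion as written. This rests on the protocol text alone and not on any figure.

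The expected frequency is low. The range of about 0.5% to 5% depends entirely on the assumed inputs and should not be read as an estimate. The case for acting rests on patient safety and ease of prevention. It should be corrected, but it does not threaten the trial's validity.

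**What to change.** Reword exclusion 6 so that it no longer relies on prior knowledge, and require that pregnancy status be established by a standard pregnancy test in patients of childbearing potential before randomisation.

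Testing before randomisation is better than testing between randomisation and infusion. A positive result in that interval would bear chiefly on patients allocated to the cells, so withdrawals would fall mainly in one arm of 12.

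The test needs a urine sample or a routine blood sample. The immune-assay sample cannot be relied on, since the protocol times it only before infusion.

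The cost is a short wording change, one inexpensive test in a minority of patients, and a brief wait for the result.

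### The primary safety outcome stops at undated, causally judged short-term side effects, and the planned 30- and 90-day morbidity calls feed no named safety outcome

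*Protocol*

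**What the plan says.** In the protocol, Methods, Outcomes, the safety part of the primary outcome reads: "Safety and tolerability of UCB cell administration (absence of immediate and short-term negative side effects". No length is given for short-term.

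Under Blinding and Randomisation, the trial is unblinded and has no placebo infusion. Controls receive standard supportive care only.

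Monitoring schedules:
- vital signs for 24 hours after infusion;
- daily symptom evaluation with the ordinal scale, until symptoms resolve or the patient dies, continued by telephone in the community;
- immune-response bloods before infusion, at 24 hours and at 7 days;
- later contact: "Follow up for other morbidities with 30- and 90-day telephonic contact will also be undertaken".

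Among the secondary outcomes, only all-cause mortality carries the 30- and 90-day time points.

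On the product, the cells come from donors ("UCB is already being collected (from healthy pregnant volunteers at term gestation"). Besides haematopoietic stem cells, the expanded product contains "but also progenitor cells, T-cell precursors and MDSCs (including pre-dendritic and pre-mast cells".

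Safety Reporting defines an adverse event without requiring a causal link and without a time limit. The DSMB reviews all categories, from AE to SUSAR.

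Under Sample size and statistics, the way forward is put thus: "This trial will help design an appropriately powered larger trial if treatment is well tolerated". Good tolerability is not defined anywhere.

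**The concern.** This is a safety and feasibility pilot, described as the first of its kind with expanded cells in COVID-19 patients. Its main product is a statement about safety. Three features of the outcome wording weaken that statement.

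1. **No window.** Read strictly, short-term excludes a delayed event. Read loosely, the boundary can be drawn after the events are known.
2. **Attribution.** A side effect of cell administration exists only once someone judges the cells to be the cause. Everyone who judges knows the arm, and controls cannot have such an event, so there is no background rate to compare with.
3. **Late data without an outcome.** The 30- and 90-day calls will produce morbidity data, but no listed safety outcome receives them.

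What is at stake is the decision on the larger trial. Tolerability is the only condition named for it, and the protocol does not say which data decide it.

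**Working it through.** The protocol gives no figure to reproduce. The sample is a convenience sample of 12 per arm, with no power, effect size or safety threshold. The check is to trace one event through the plan.

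**Trace.** Take a new, non-fatal complaint at day 45 in an infused patient whose pneumonia symptoms have resolved. It is reported at the 90-day call.

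- *Primary safety outcome:* counted only if day 45 is taken as short-term and the complaint is judged to be caused by the cells. The protocol settles neither.
- *Primary ordinal scale:* daily classification has ended, because symptoms resolved.
- *Secondary outcomes:* mortality does not apply. Ventilation and culture-positive bacterial infection carry no stated window and would catch only events of those kinds. Stability, symptom resolution, imaging and cytokines do not describe a new late complaint.
- *Adverse event definition:* met, with no attribution needed. The event goes to the DSMB.
- *Condition for the larger trial:* undefined, so the event may or may not weigh.

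Now take the same complaint in a control patient. It cannot be a side effect of the cells, so the primary safety outcome has no place for it. The adverse event definition speaks of participants given a medicinal or biological product, so its reach in the control arm is also unclear. No between-arm comparison of late events follows from the text.

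**How often the classification would matter.** The protocol gives no risk of delayed events, so the risk p is an assumption. With n = 12 infused patients, the chance of at least one such event is 1 − (1 − p)^12:

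- p = 1%: 1 − 0.99^12 = 0.114, or 11%;
- p = 5%: 1 − 0.95^12 = 0.460, or 46%;
- p = 10%: 1 − 0.90^12 = 0.718, or 72%.

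These are chances that an event occurs, whichever outcome it is filed under. They do not measure the wording fault. They show only that the filing question could well arise.

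**What the fix cannot do.** If none of the 12 has an event, the one-sided 95% upper limit for the true risk is 1 − 0.05^(1/12) = 0.221, or 22%. A longer window closes the gap in the definition but does not let 12 patients exclude uncommon delayed harm.

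**Timing.** At the expected 4 to 6 patients a month, 24 patients take 24/6 = 4 to 24/4 = 6 months. Adding 90 days (about 3 months) puts the last day-90 contact at about 7 to 9 months, inside the 12 months set for the final report. If recruitment takes the full 12 months allowed, the last contact falls at about 15 months. Because 90-day mortality is already an outcome, that wait exists in the present plan.

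**The case against.** The strongest answer is that late events are not lost. Symptoms are evaluated daily until they resolve, calls follow at 30 and 90 days, mortality is recorded at both, and the DSMB receives every adverse event within a week with no time limit. Its members include a scientist familiar with cell-based therapies. All of this stands. It would be wrong to say that 24 hours of vital signs is the only scheduled safety measurement, or that the DSMB would not see delayed harm. But DSMB review protects patients during the trial. It does not define the safety result that is reported or the meaning of good tolerability.

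A second answer is that a statistical analysis plan, not shown here, could set the number of days. It could. The attribution-based wording and the calls without an outcome would remain, and both are fixed in the protocol's own outcome list.

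A third is that counting every adverse event to day 90 in patients hospitalised with COVID-19 mixes illness with infusion effects. That is fair. It is a reason to keep early infusion reactions as a separate, visible subset, and to use the control arm for comparison. Whether the wider count is labelled primary or is a named safety outcome beside it is open to debate.

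Two stronger readings are tempting and should be resisted. A reader might infer that the protocol itself names GVHD as a hazard of this infusion. It does not. The text presents it as a benefit, "as demonstrated by the reduction of the risk to severe acute and chronic GVHD", and the setting is transplantation: "results of a Phase I/II trial of cord blood transplantation of expanded UCB cells have recently been published (25". A reader might also infer that the primary safety outcome alone decides on the larger trial. The protocol says only that the treatment must be well tolerated, and nothing prevents later data from informing that judgement. The fault is that nothing requires it.

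**Conclusion.** The point holds in limited form. The primary safety outcome is undated, rests on an unblinded causal judgement and has no control-arm counterpart. The planned late morbidity calls are tied to no named safety outcome. A non-fatal delayed event can therefore be known to the DSMB and still be absent from every reported safety outcome and from the tolerability judgement.

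The size cannot be put as a bias in an estimate, because the analysis is descriptive. The 11% to 72% range rests wholly on assumed risks of 1% to 10%, and on all 12 patients being infused and followed. That delayed events are a reasonable question here rests on the product being donor-derived, expanded and, by the protocol's account, containing stem cells and T-cell precursors. It does not rest on any hazard that the protocol declares.

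This should be corrected before recruitment. It is a defect of outcome definition, not a failure of safety oversight.

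**What to change.** 1. Keep early infusion reactions as a stated subset of the safety outcome, with the window given in days.
2. Add a named safety outcome: all AEs and SAEs in both arms, from randomisation to day 90, using the protocol's own attribution-free definition. State that the definition applies to controls too.
3. Replace the open question on other morbidities at the 30- and 90-day calls with a fixed checklist, asked identically in both arms. It should include symptoms of delayed donor-cell reactions, with the items chosen by the clinical investigators.
4. State that tolerability, as the condition for the larger trial, is judged on both the early subset and the day-90 outcome.

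The cost is a protocol amendment and a one-page checklist on contacts already planned, with no extra patients or visits. More illness-related events will be counted, and in 24 patients the control arm gives only a rough comparison. The final safety result waits for the last day-90 call, as 90-day mortality already does.
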